Interim analyses will not be conducted to evaluate conditional power (futility) or efficacy, thus preserving the overall Type-I error probability regarding the efficacy of the intervention. Given the nature of an elderly study population, we expect study attrition in the form of participant death or withdrawal. Our proposed analysis plan using mixed effects models are robust under the missing at random (MAR) assumption that the probability for dropping out depends on participants’ characteristics and medical conditions. We will compare patients’ characteristics between the completers and non-completers to detect potential violation to the missing at random assumption. We will conduct sensitivity analyses to assess the potential impact of missing data using multiple imputation which allows the imputation of missing outcomes for those who drop out using data gathered from these patients at baseline and prior to drop-out. We will use SAS software version 9.4 (SAS Institute, Cary, North Carolina) or relevant updated versions for all analyses.

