### Sample Size and Rationale

The sample size calculation was conducted using a mixed effects model and adjusting for the cluster randomization design. Assuming a within-subject correlation of 0.3, 0.2 and 0.1 for outcomes observed 6, 12 and 18 months apart, respectively, from the same individuals over time, 96 patients per group is required for 80% power to detect differences in composite cognitive scores of 0.6 SD at 24 months between the intervention and usual care groups with type I error rate at α=0.05 assuming linear trends in cognitive change in both groups. We further assume an intra-class coefficient (ICC) of 0.05 for primary care physicians and an average of 6 patients per physician. Accounting for the cluster design requires 120 patients per group to complete the trial. With an expected 30% attrition rate, we plan to enroll 172 patients per group into the study. Prior studies have reported mean differences in 1-year change of cognitive scores of 1.82 (SD 17) or 1.93 (SD 15) between those on definite anticholinergics versus those non-users. The effect sizes we used assume that our intervention will be able to detect a one-sixth reduction in expected cognitive decline if patients in the intervention group discontinue anticholinergics. Our assumption on the ICC is based on prior studies on prescribing patterns in physicians and practices.^58^

In Primary Aim 2, using the effective sample size of 96 patients per group accounting for the design effect from cluster randomization, we will have 85.6% power to estimate the confidence bands with half-width of 0.3 SD for the differences in symptom scores from PROMIS and HUI scores between the intervention and usual care groups during follow-up using the two-sample t-tests at the 0.05 level. Power estimates were calculated using the GLMPower and Power procedures in SAS software version 9.4 (SAS Institute, Cary, North Carolina).

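### Comparing completers with non-completers cannot test missing at random, and the only sensitivity analysis named makes the same assumption, with 30% attrition expected

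*Protocol article*

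**What the plan says.** The Analysis Plan expects losses from two sources: "we expect study attrition in the form of participant death or withdrawal". It calls the mixed models "robust under the missing at random (MAR) assumption that the probability for dropping out depends on participants’ characteristics and medical conditions". Two safeguards follow.

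- **A check of the assumption.** The plan will compare patients' "characteristics between the completers and non-completers to detect potential violation to the missing at random assumption".
- **A sensitivity analysis.** "We will conduct sensitivity analyses to assess the potential impact of missing data using multiple imputation", described as allowing the "imputation of missing outcomes for those who drop out using data gathered from these patients at baseline and prior to drop-out".

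No other missing-data analysis is named. Sample Size and Rationale gives the scale: "Accounting for the cluster design requires 120 patients per group to complete the trial", and "With an expected 30% attrition rate, we plan to enroll 172 patients per group into the study".

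**The concern.** MAR allows dropout to depend on anything observed and conditioned on. The plan describes MAR in just those terms, as dropout that depends on characteristics and medical conditions. It then treats a difference in those same characteristics as a sign that MAR is violated. Such a difference contradicts missing completely at random, which is a stronger assumption that the mixed model does not need. What would undermine the model is dropout that depends on the unseen score after allowing for the observed data, and no comparison of observed characteristics can reveal that.

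The imputation does not close the gap. It fills in missing scores from each dropout's own earlier data, so it too assumes that people who left resemble people who stayed with the same history. Agreement between the two analyses would say little about whether that assumption is true.

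At stake is what the trial can claim about robustness. Intervention participants have pharmacist contact and may stop a medication, while usual-care participants receive mailed material. Reasons for leaving could therefore differ by arm, although the article reports no evidence that they do. As written, the check could raise an alarm where there is no bias and give reassurance where there is.

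**Working it through.** **1. Reproduce the plan's enrolment figure.** Inputs from Sample Size and Rationale: 96 per group before clustering, ICC 0.05, 6 patients per physician, 30% attrition.

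- Design effect: 1 + (6 − 1) × 0.05 = 1.25
- Completers per group: 96 × 1.25 = 120
- Enrolled per group: 120 / (1 − 0.30) = 171.4, rounded up to 172

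Both stated figures are reproduced. Expected losses are 0.30 × 344 ≈ 103 participants.

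**2. Can the comparison detect a failure of MAR?** This was checked by a large simulation (n = 400,000).

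- From the document: correlations of 0.3, 0.2 and 0.1 at 6, 12 and 18 months apart, a true difference of 0.6 SD at month 24, and 30% missing.
- Assumed: all dropout just before month 24, a correlation of 0.05 at 24 months apart, a linear rise in effect from 0.15 to 0.6 SD, and the dropout mechanisms below.
- Estimator: arm-specific regression imputation from observed history, the large-sample limit of MAR-based imputation or likelihood.

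| Dropout mechanism | Baseline difference in cognition, completers minus non-completers | Estimate (truth 0.60) | Bias |
|---|---|---|---|
| MAR: depends on baseline and month-18 scores | 0.85 SD | 0.60 | 0.00 |
| Not MAR: in usual care, depends on the part of the month-24 score not explained by history | 0.00 SD | 0.37 | −0.23 SD |

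The comparison flags a large difference where the estimate is unbiased and none where it is biased. MAR-based imputation does not remove the bias. The size of −0.23 SD belongs to the assumed mechanism, but the logic is general.

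**3. How much do earlier scores say about a missing month-24 score?** Regress month 24 on months 6, 12 and 18 with the plan's correlations. Baseline is left out because no correlation 24 months apart is given.

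- Coefficients: about 0.012, 0.118 and 0.262
- R² = 0.012 × 0.1 + 0.118 × 0.2 + 0.262 × 0.3 ≈ 0.103

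On the plan's own assumptions, about 90% of the variance of the missing score is not explained by earlier follow-up scores.

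**4. Size of a departure.** Let p be the proportion missing in an arm and δ the amount by which dropouts there differ from their MAR prediction. The shift in the 24-month difference is p_I × δ_I − p_C × δ_C, for intervention and control. With p = 0.30 and a departure in one arm only:

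| Assumed departure | Shift | Share of 0.6 SD |
|---|---|---|
| 0.3 SD | 0.30 × 0.3 = 0.09 SD | 15% |
| 0.5 SD | 0.30 × 0.5 = 0.15 SD | 25% |

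- With equal p and equal δ in both arms the terms cancel.
- For an effect averaged over visits the shift is smaller. If attrition accrued linearly (an assumption), missingness would be 7.5, 15, 22.5 and 30%, with mean 18.75%, and the 0.3 SD case gives 0.1875 × 0.3 ≈ 0.056 SD.

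**The case against.** Several points on the other side have force.

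- **The comparison is not useless.** MAR always holds or fails relative to what the model contains. The primary model includes group, time, their interaction, baseline cognition and only those baseline factors that differ between arms. If non-completers differ on a predictor of cognition outside that set, MAR as this model uses it is in doubt, and the comparison would show it. This stands, and it is the right use of the comparison. It does not reach dropout that depends on unobserved scores.
- **The imputation need not repeat the primary estimate.** Its description could cover PROMIS, HUI and self-reported medications, which are collected at every visit and are not in the primary model. A reader might infer that it will simply reproduce the primary result, but the article does not show that. It remains an analysis under MAR.
- **Further analyses may be specified elsewhere.** This is a condensed article and an analysis plan may exist. The fair statement is that no other analysis is named. That does not rescue the check, whose stated purpose is wrong as printed.
- **Imputation after death is not stated.** Death is counted as attrition and imputation is for those who drop out, so a reader might infer that scores would be imputed after death. The text is ambiguous and does not say so.
- **A larger relative size is tempting.** The one-year differences cited in the article are 1.82/17 = 0.107 and 1.93/15 = 0.129 SD. Doubling them to 24 months would make the same shifts look like a third to two thirds of the effect. The article gives no 24-month figure from those studies, and the doubling assumes linear accrual. The document's own yardstick is 0.6 SD.
- **Assessors are blinded.** This limits bias in measurement but does not prevent withdrawal related to arm.

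**Conclusion.** The point holds. The completer comparison is given a purpose it cannot serve, and the only sensitivity analysis named stays within MAR although about 103 of 344 participants are expected to be lost.

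The illustrated effect is a shift of 0.09 to 0.15 SD in the 24-month difference, 15% to 25% of the design effect. It rests on assumed departures of 0.3 to 0.5 SD in one arm and on the departure applying to the full 30%, which includes deaths. It would be smaller for an effect averaged over visits and could be nil if the arms behave alike.

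None of this makes the mixed model a wrong choice for the primary analysis or shows that the result will be biased. The defect is that the stated safeguards could not tell a reader whether it is. It should be corrected before outcomes are analysed by arm.

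**What to change.** - **Restate the comparison.** Describe dropout by arm and by reason, with deaths shown separately. Use it to choose covariates or auxiliary variables, and remove the claim that it detects a violation of MAR.
- **Add an analysis that departs from MAR.** Use delta-adjusted multiple imputation with delta varied separately in each arm, and report the values at which the conclusion changes (a tipping-point analysis). Fix the range of deltas, with reasons, before outcomes are seen by arm.
- **Specify the imputation model.** It should respect clustering by primary care physician and use the PROMIS, HUI and medication data already collected. The existing MAR imputation then becomes the case with delta zero in both arms.
- **Clarify deaths.** State that cognitive scores after death are not imputed.

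The cost is revised wording and a little extra programming. No new data are needed, and the primary model and sample size are unchanged.

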### Sample Size and Rationale

The sample size calculation was conducted using a mixed effects model and adjusting for the cluster randomization design. Assuming a within-subject correlation of 0.3, 0.2 and 0.1 for outcomes observed 6, 12 and 18 months apart, respectively, from the same individuals over time, 96 patients per group is required for 80% power to detect differences in composite cognitive scores of 0.6 SD at 24 months between the intervention and usual care groups with type I error rate at α=0.05 assuming linear trends in cognitive change in both groups. We further assume an intra-class coefficient (ICC) of 0.05 for primary care physicians and an average of 6 patients per physician. Accounting for the cluster design requires 120 patients per group to complete the trial. With an expected 30% attrition rate, we plan to enroll 172 patients per group into the study. Prior studies have reported mean differences in 1-year change of cognitive scores of 1.82 (SD 17) or 1.93 (SD 15) between those on definite anticholinergics versus those non-users. The effect sizes we used assume that our intervention will be able to detect a one-sixth reduction in expected cognitive decline if patients in the intervention group discontinue anticholinergics. Our assumption on the ICC is based on prior studies on prescribing patterns in physicians and practices.^58^

In Primary Aim 2, using the effective sample size of 96 patients per group accounting for the design effect from cluster randomization, we will have 85.6% power to estimate the confidence bands with half-width of 0.3 SD for the differences in symptom scores from PROMIS and HUI scores between the intervention and usual care groups during follow-up using the two-sample t-tests at the 0.05 level. Power estimates were calculated using the GLMPower and Power procedures in SAS software version 9.4 (SAS Institute, Cary, North Carolina).

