### Randomization procedures

In this cluster randomized trial, randomization occurs at the level of primary care provider in a 1:1 proportion between intervention and usual care using a randomization list with a computer-generated random scheme in random blocks of 4 or 6 stratified by healthcare system. Research staff are blinded to provider allocation status at the time of recruitment and throughout the study to avoid bias in data collection.

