### Analysis Plan

The cluster randomized trial design will be used by randomizing primary care physicians (PCP) into the intervention or usual care arms. Outcomes will be collected and analyzed at the patient level. We will examine assigned randomization against the computer-generated randomization scheme to ensure randomization validity. Patient characteristics between the two groups will be compared using mixed effects models for continuous variables and generalized estimating equations for categorical variables while adjusting for random PCP effects. We will examine the distributions of continuous variables and use alternative approaches such as transformation or nonparametric methods in cases of violation to the normal distribution assumption. We will also examine the frequency distribution of all categorical variables and adopt exact inference procedures in cases of zero or small cell size. Any baseline variable that is found to be significantly different between the two groups will be included as a covariate in the analyses outlined below.

An intension to treat approach will be used in the analysis of all outcome measures. Composite cognitive scores collected at 6, 12, 18 and 24 months will be used as the primary outcome variables in mixed effects models. An indicator variable for intervention group (intervention vs usual care), time, interaction between group and time, and baseline cognitive scores will be included as independent variables as well as significant factors from the baseline comparison. PCP will be used as random effects to adjust for within-physician correlations. Significant group and time interaction or significant group main effect will indicate differences in cognitive function between the two groups. If significant interactions between group and time are found, post-hoc analyses will be conducted to determine the times when the two groups have significantly different cognitive scores. A significant main group effect in the absence of a group-by-time interaction would indicate differences between groups in cognitive function at all follow-up time points.

In a second set of models, we will determine whether differences between groups were accounted for by decreases in total exposure to anticholinergics from baseline to 24 months. For each medication, standardized daily exposure will be calculated using standardized daily dose as in the study by Gray^7^ and validated in our prior work^14
17

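### From the printed inputs, 96 per group does not give 80% power at 0.6 SD for the main effect, the group-by-time test or the 24-month difference

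*Protocol article*

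**What the plan says.** Sample Size and Rationale says that "96 patients per group is required for 80% power to detect differences in composite cognitive scores of 0.6 SD at 24 months". The inputs it prints are:

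- Correlation: "Assuming a within-subject correlation of 0.3, 0.2 and 0.1 for outcomes observed 6, 12 and 18 months apart".
- Error rate and trajectory: "with type I error rate at α=0.05 assuming linear trends in cognitive change in both groups". Sidedness and visit means are not given.
- Clustering: "We further assume an intra-class coefficient (ICC) of 0.05 for primary care physicians and an average of 6 patients per physician".

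It then inflates to 120 completers and 172 enrolled per group, which is 344 in all.

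The Analysis Plan fixes the outcome visits: "Composite cognitive scores collected at 6, 12, 18 and 24 months will be used as the primary outcome variables in mixed effects models". It also fixes the rule for a positive result: "Significant group and time interaction or significant group main effect will indicate differences in cognitive function between the two groups". Comparisons at single visits are post hoc and follow only a significant interaction.

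**The concern.** The two tests in the decision rule measure different things. The main effect averages the group difference over four visits, and the interaction measures how that difference changes between visits. Under one trajectory they generally have different power, so a single 80% can describe at most one of them. The article does not say which. The sentence is worded as a difference at 24 months, which is a third quantity.

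The base figure of 96 carries through to 120, 172 and 344, and it returns as the effective sample size for the quality-of-life and symptom outcomes. A reader who meets a null interaction or a null main effect will judge it against the stated 80%. If the true values are near 98% for one test and 49–66% for the other, that judgement is wrong in opposite directions for the two tests.

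**Working it through.** **Inputs.** From the article: 96 per group; 0.6 SD at 24 months with SD = 1; correlations 0.3, 0.2 and 0.1 at lags of 6, 12 and 18 months, which are the lags among four follow-up visits; α = 0.05; 1:1 allocation; ICC 0.05; 6 patients per physician; 30% attrition. Assumed: two-sided testing, and groups equal at baseline and diverging linearly. The differences are then 0.15, 0.30, 0.45 and 0.60 SD at months 6, 12, 18 and 24.

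**The later steps reproduce.** Design effect = 1 + (6 − 1) × 0.05 = 1.25. Then 96 × 1.25 = 120, and 120 / 0.7 = 171.4, so 172. Any discrepancy lies in the 96 itself.

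**Method.** For a contrast with standardised difference δ, the normal approximation for 80% power is n per group = 2(1.96 + 0.8416)² / δ² = 15.70 / δ². Power at n = 96 is approximately Φ(δ√48 − 1.96). The table gives the noncentral-F or t results, which differ slightly.

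1. *24-month difference.* δ = 0.6, so n = 15.70 / 0.36 = 43.6, or 45 with t. Power at 96: 0.6 × 6.928 = 4.157, and Φ(4.157 − 1.96) = 0.986, or 98.5% with t. Neither the other visits nor the correlations enter. The effect detectable with 80% power at n = 96 is 2.80 × √(2/96) = 0.404 SD, or about 0.41 SD with t.
2. *Group main effect (mean of four visits).* Difference = 1.5 / 4 = 0.375. Variance = [4 + 2(3 × 0.3 + 2 × 0.2 + 0.1)] / 16 = 0.425. δ = 0.375 / √0.425 = 0.575, so n = 47.4, or 49 with t.
3. *Linear group-by-time, weights (−3, −1, 1, 3).* Difference = −0.45 − 0.30 + 0.45 + 1.80 = 1.5. Variance = 20 + 3.0 − 2.4 − 1.8 = 18.8. δ = 1.5 / 4.336 = 0.346, so n = 131, or 133 with t.
4. *3-df group-by-time (time as categories).* The squared standardised distance of the three visit-to-visit differences is 0.1198, so the noncentrality at n = 96 is 48 × 0.1198 = 5.75 on 3 df.

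| Test | Power at 96 per group | n per group for 80% |
|---|---|---|
| 24-month difference | 98.5% | 45 |
| Group main effect | 97.8% | 49 |
| Linear group-by-time | 66.4% | 133 |
| 3-df group-by-time | 49.0% | 185 |

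**Variants, to see whether 96 appears.**

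- Univariate repeated-measures interaction: 58–59% power, n = 150–152.
- Adjusting for baseline: about 98% for the main effect, 98.5% at 24 months, 50–69% for the interaction.
- One-sided 0.05, linear interaction: 77%.
- Baseline as a fifth outcome visit, with the lag-24 correlation set between 0 and 0.1: n = 73–80 (linear), 85–89 (univariate), 112–121 (multivariate).
- No difference at month 6: n = 75 (linear), 85–86 (univariate), 105 (3-df).
- Linear rise from 0.07 SD at month 6: contrast = 10 × (0.53 / 3) = 1.767, and δ = 1.767 / 4.336 = 0.407. This gives n = 94.6, or 96 with t, for the linear interaction. The main effect then has 94% power.
- 96 read as a total, so 48 per group: 79.6% for the main effect under the linear-from-baseline trajectory.

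**The case against.** The strongest reply is that equal groups at baseline is my assumption and not a printed input. The article says only "assuming linear trends in cognitive change in both groups". If the groups began to separate about 3.6 months after baseline, the month-6 difference would be 0.07 SD and the linear interaction would need exactly 96. The other interaction variants fall on both sides of 96, which fits a group-by-time calculation whose visit means were left out of a condensed article. This stands as a limit on the finding. It rules out saying that no linear trajectory can yield 96, and it makes the 49–66% conditional. It does not rescue the figure as printed. No such month-6 value is stated, equal baselines are the natural reading in a randomised trial, and even at 0.07 SD the main effect has 94% power and the 24-month difference 98.5%.

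A second reply is that the 24-month comparison is only post hoc in the Analysis Plan, so excess power there does not prove that a mixed-model calculation was wrong. That is fair. It is included because the sample-size sentence is worded in those terms.

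Two stronger readings are tempting, and the documents support neither. A reader might infer that the trial is underpowered. Its rule is satisfied by either test, so on these inputs the power to meet it is at least the main effect's 97.8%. A reader might also argue that an effect which appears early and stays flat leaves the interaction with only 5% power. In that case there is no interaction to find and 5% is simply α. The main-effect half of the rule covers it.

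**Conclusion.** The point holds in a limited form. The stated 80% at 96 per group does not follow from the printed inputs for either test in the decision rule, or for the 24-month difference that the sentence names. The 24-month result (98.5%; 45 per group for 80%) does not depend on the trajectory. The main-effect result (97.8%; 49) and the interaction results (66.4% linear, 133; 49.0% on 3 df, 185) rest on groups equal at baseline, linear divergence to 0.6 SD, SD = 1 and two-sided 0.05. The interaction figures are the most sensitive to the assumed month-6 difference.

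The match at 48 per group might lead a reader to conclude that 96 is a mislabelled total. It is worth checking, but it is an inference from a numerical match. The document calls 96 a per-group figure throughout, and a small month-6 difference is another possible origin.

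**What to change.** In Sample Size and Rationale:

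1. State which test the 96 was computed for and the group difference assumed at each visit.
2. Check the original power output to see whether 96 was per group or total, and correct the label if needed.
3. Restate power at an effective 96 per group separately for the main effect and for group-by-time. Under linear divergence from equal baselines these are about 98%, and about 66% (linear) or 49% (3-df). If another trajectory was intended, print it with its own figures.
4. If the 24-month wording stays, add that 96 per group gives 98.5% power for 0.6 SD and 80% for about 0.41 SD.

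The cost is a text change and one rerun of the power calculation. Enrolment stays at 344, of which about 328 had been recruited when the article was drafted. The primary analysis and its decision rule stay as written. Replacing them with a single 24-month test would be a separate design change and is not needed to correct this figure.

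### The 0.6 SD planning effect is 2.3 to 2.8 times the two-year difference implied by the figures cited for it, and the one-sixth sentence does not connect them

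*Protocol article*

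**What the plan says.** All the relevant statements are in the article's Sample Size and Rationale section.

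- **Target:** the calculation is said "to detect differences in composite cognitive scores of 0.6 SD at 24 months", with "96 patients per group is required for 80% power" and "type I error rate at α=0.05".
- **Model:** a mixed effects model, "assuming linear trends in cognitive change in both groups", with correlations of 0.3, 0.2 and 0.1 between outcomes 6, 12 and 18 months apart.
- **Cited evidence:** prior studies with "mean differences in 1-year change of cognitive scores of 1.82 (SD 17) or 1.93 (SD 15" in the second case, comparing definite anticholinergic users with non-users.
- **Link from evidence to target:** "The effect sizes we used assume that our intervention will be able to detect a one-sixth reduction in expected cognitive decline", on the condition that intervention patients stop their anticholinergics.

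The section does not put a figure on the expected decline and shows no step from the cited differences to 0.6 SD.

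**The concern.** The sentences are presented as target, evidence and link, yet the evidence is much smaller than the target and the link does not join them. The 80% power claim therefore refers to an effect well above the one the section offers as its rationale.

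This bears on what the trial can conclude. The Background and Discussion present it as a test of whether the association between anticholinergics and cognition is causal. If an effect of the cited size were real, a non-significant result would still be more likely than not under the calculations below. A reader who takes the one-sixth sentence at face value would believe that the design covers a small fractional effect with 80% power.

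**Working it through.** **1. The plan's own figures.** Inputs from Sample Size and Rationale: 96 per group before clustering, ICC 0.05, 6 patients per physician, 30% attrition.

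- Design effect: 1 + (6 − 1) × 0.05 = 1.25, and 96 × 1.25 = 120. Reproduced.
- Attrition: 120 / 0.70 = 171.4, rounded up to 172. Reproduced.
- The 96 itself is not matched exactly. The tested contrast is not stated, and standard repeated-measures variants with the stated correlations fall on both sides of 96 (from 49 for some group main effects to 185 for some interaction or slope tests). The 96 is therefore taken as given and is not disputed.

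**2. The cited differences in SD units.**

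| | One year | Two years, linear (×2) | 0.6 ÷ two-year value |
|---|---|---|---|
| 1.82 / 17 | 0.107 | 0.214 | 2.80 |
| 1.93 / 15 | 0.129 | 0.257 | 2.33 |

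The doubling follows the plan's linear-trend assumption. Without it the cited effect is smaller, 0.11 to 0.13 SD.

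**3. Does a change of scale close the gap?** Two conversions were tried.

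- *The cited SDs are SDs of change.* With equal variances, multiply by √(2(1 − ρ)), where ρ is the correlation between a person's scores at the two times. The values of ρ are assumptions, except that 0.2 is the plan's own 12-month value. Results: 0.14 to 0.16 (ρ = 0.8), 0.21 to 0.26 (0.5), 0.27 to 0.33 (0.2), 0.30 to 0.36 (0). Even ρ = −1 gives only 0.43 to 0.51.
- *The composite is an average of z-scores, so its SD is below 1.* For k tests with mean inter-test correlation r, the SD is √((1 + (k − 1)r)/k). Assuming k = 4 or 5 and r from 0.2 to 0.6, the SD is 0.60 to 0.84. Dividing 0.214 and 0.257 by it gives about 0.26 to 0.43.

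Taken singly, plausible conversions span about 0.14 to 0.43 SD. Stacking both with the plan's ρ = 0.2 and the most favourable composite (k = 5, r = 0.2, SD 0.60) gives 0.271/0.60 = 0.45 to 0.326/0.60 = 0.54. Only with ρ = 0 as well does the upper figure reach about 0.61 (0.364/0.60).

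**4. The one-sixth sentence.**

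- Literally: if 0.6 SD is one-sixth of the expected decline, that decline is 0.6 × 6 = 3.6 SD in two years, in people enrolled without a dementia diagnosis.
- One-sixth of the cited two-year difference: 0.214/6 = 0.036 and 0.257/6 = 0.043 SD. This is one reading only, because expected decline is never quantified.

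**5. Power at the cited effects** (two-sided α = 0.05 assumed, since sidedness is not stated).

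- *Plan's calculation scaled.* 80% power at 0.6 SD corresponds to a standardised signal of 1.960 + 0.842 = 2.802. At 0.214 SD this becomes 2.802 × 0.214/0.6 = 1.00, power 17%. At 0.257 SD it becomes 1.20, power 22%. This treats the test as a single-contrast normal test.
- *Simple t-test at 24 months, effective 96 per group.* Noncentrality d√(96/2): power 31% at 0.214 SD and 43% at 0.257 SD.

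**The case against.** Several points on the other side have force.

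- **A planning effect may simply be chosen.** A design can target 0.6 SD as the effect it is able to detect. That stands. The fault is in presenting the cited studies and the one-sixth statement as its basis.
- **0.21 to 0.26 SD is not a ceiling.** A reader might infer that 0.6 SD exceeds anything deprescribing could achieve. The documents do not support that. The cited figures are differences in one-year change and do not capture deficit already accumulated in existing users, and the conceptual model in the Background allows for improvement as well as preservation. Nor is 0.21 to 0.26 SD a settled benchmark, because the instruments and the meaning of the SDs are not given. It should not be fixed as a margin for judging the trial's confidence interval.
- **The t-test is not the plan's test.** A reader might compute that 96 per group gives 80% power at about 0.41 SD and restate the design that way. The same t-test gives 98.5% power at 0.6 SD rather than the stated 80%, so it is not the plan's calculation, and the restatement would make the claim more favourable. Baseline adjustment, which the Analysis Plan includes, may raise power above the figures shown, by an amount the document does not allow one to fix.
- **The 0.04 SD reading may be unfair.** The sentence may be garbled: 0.6/0.107 = 5.6, so it could invert a ratio. That is conjecture, but it is a reason not to rest the point on 0.04 SD.
- **The harm is not written in the document.** It nowhere says that a null result will be read as evidence against causation. Recruitment was also nearly complete, at about 328 of 344.
- **The full protocol may hold a derivation.** It may, but the point concerns what is printed: a justification that the adjacent numbers contradict.

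**Conclusion.** The stated basis for the primary power claim is wrong as written. The 0.6 SD target is 2.3 to 2.8 times the two-year difference implied by the cited studies, and the one-sixth sentence fits neither the target nor the evidence. This rests on linear accrual over two years, which is the plan's assumption, and on the cited SDs serving as the standardising scale. Relaxing the second moves the benchmark within about 0.14 to 0.43 SD for any single plausible conversion. Reaching 0.6 needs two conversions stacked at favourable extremes, including zero correlation between a person's scores a year apart, where the plan assumes 0.2.

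Power at 0.21 to 0.26 SD is about 17 to 22% on the plan's own scaled calculation and about 31 to 43% on a simple t-test. On either figure, a non-significant result would not by itself exclude an effect of the cited size.

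Two stronger conclusions a reader might draw are not supported: that the 96 per group is miscalculated, and that the trial cannot detect a real benefit. The inflation to 120 and 172 is correct, and a true effect near 0.6 SD would be detected with the stated power if the plan's calculation is accepted.

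**What to change.** In Sample Size and Rationale:

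1. Delete the one-sixth sentence, or replace it with a stated expected two-year decline, in SD units of the composite, from which 0.6 SD follows.
2. Describe 0.6 SD as the effect the design detects with 80% power under the stated mixed-model calculation, and say that it exceeds the 0.21 to 0.26 SD implied by the cited studies under linear accrual.
3. Name the contrast on which the calculation rests and report power at 0.21 and 0.26 SD under that same model, with any gain from baseline adjustment and its assumptions shown.
4. State that a non-significant primary result will be interpreted from its 95% confidence interval and does not by itself exclude an effect of the cited size.

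The cost is a few sentences and a less favourable power statement. No patients, assessments or analyses are added, and the change can be made before data collection ends (expected July 2026).
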